### 2.7. Routine intervention group

Regular obstetric exams, departmental pregnancy awareness booklets, routine health education about emotions, diet, sleep, and other pregnancy-related topics, as well as routine health education will be given to the subjects.

At 11 to 13 weeks in the first trimester, 19 to 21 weeks in the second trimester, and 27 to 29 weeks in the third trimester, the individuals in both groups will complete the electronic questionnaire survey that asked about their levels of anxiety and sadness.

### 2.8. Outcomes

After participant enrollment, baseline evaluations will be done, then participants will have follow-up appointments at 11 to 13 weeks in the first trimester, 19 to 21 weeks in the second trimester, and 27 to 29 weeks in the third trimester. Additionally, 2 groups of people will receive electronic questionnaires for anxiety and depression levels to gauge the effectiveness of the intervention. Primary endpoint measures are improvements in anxiety and depression (i.e., overall effectiveness rate, defined as the proportion of patients with a decreases of more than 25% in SAS^[40]^ and SDS^[41]^ scores following the abovementioned intervention). At each follow-up, the anxiety and depression ratings of the 2 groups are compared horizontally, and the simultaneous effects of the 2 interventions on the subjects’ anxiety and depression are compared. The anxiety and depression ratings of the 2 groups are longitudinally compared after all the follow-up have been completed, and the effects of the 2 interventions on the participants’ anxiety and depression before and after the interventions are compared. The secondary outcomes are comparisons of pregnancy outcomes, including ectopic pregnancy, miscarriage, as well as live birth. Ectopic pregnancy is defined as the development of the fertilized egg outside the uterine cavity; miscarriage is defined as termination of pregnancy at less than 28 weeks of gestation with a fetus weighing less than 1000 g; live birth is defined as at least 22 weeks of gestation or at least 500 g.

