## Abstract

**Methods and Analysis::**

In the present randomized controlled study, 296 patients with confirmed clinical pregnancy following IVF-ET will be randomly assigned to receive standard intervention support or WeChat peer support on a 1:1 basis. The levels of anxiety and depression are the primary endpoints. Assessments will be performed at baseline measurements, first trimester, second trimester, and third trimester, and data will be collected.

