## 2. Methods and analysis

### 2.1. Study design

A randomized control trial design will be used in this study. It is anticipated that recruitment at the Reproductive Center of Integrated Medicine, Affiliated Hospital of Shandong University of Traditional Chinese Medicine (SDUTCM) will begin in December 2022 and last through December 2023 for women with confirmed clinical pregnancy undergoing IVF-ET. Writing this guideline, we adhered to SPIRIT’s suggestions.^[38]^ Figure 1 displays the research flow chart, and Table 1 displays the research process timetable.

**Table 1 T1:** Example template of recommended content for the schedule of enrolment, interventions, and assessments. *

Outcome	Assessment	Baseline	11–13 wks gestation	19–21 wks gestation	27–29 wks gestation	Within 3 d after delivery

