### 2.11. Sample size calculation

Overall effectiveness rate is defined as the proportion of patients whose SAS and SDS scores have reduced by more than 25%, the primary endpoint of the study. Based on previous clinical experience in our center, at the third follow-up visit, we found that the overall effectiveness rate was approximately 75% in the WeChat peer support group and about 60% in the routine intervention group. A total of 236 patients were enrolled in the study utilizing the PASS 15 procedure (NCSS, LLC. Kaysville, Utah), with a hypothesis test level of 0.05 and a test power of 0.8. After accounting for the 20% dropout rate, 296 patients with 148 in each group comprised the final sample size.

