### 2.12. Statistical analysis

The SPSS 26.0 software was used to analyze all the data (SPSS Inc., Chicago, IL). The data’s normality was evaluated using the Shapiro–Wilk test. Depending on the distribution’s normality, quantitative variables were examined using the independent samples t-test or Mann–Whitney *U* test and represented as mean standard deviation (SD) or median (interquartile range, IQR). Frequencies and percentages are used to express qualitative characteristics. Comparing categorical variables was done using the 2 test or Fisher’s exact test. In all statistics, a 2-tailed alpha of 0.05 was employed.

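### The primary endpoint is not stated consistently: score levels or a >25% responder rate, one combined rate or two, no visit fixed, and three or four follow-up measurements

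*Protocol article*

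**What the plan says.** The protocol article describes the primary endpoint in four places.

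- **Abstract, Methods and Analysis:** "The levels of anxiety and depression are the primary endpoints". This is plural and refers to levels. Assessments are at baseline and in the three trimesters.
- **Section 2.1, Table 1:** anxiety level (SAS) and depression level (SDS) stand under the primary outcome heading. Both are ticked at baseline, at the three pregnancy visits, and in a further column, "Within 3 d after delivery".
- **Section 2.8:** improvement in anxiety and depression, that is, the "overall effectiveness rate, defined as the proportion of patients with a decreases of more than 25% in SAS" and SDS. The only timing is that it follows the intervention. The section then adds: "At each follow-up, the anxiety and depression ratings of the 2 groups are compared horizontally", and a longitudinal comparison once follow-up is complete. Only pregnancy outcomes are called secondary. Three follow-ups are listed (11-13, 19-21 and 27-29 weeks), as in section 2.7.
- **Section 2.11:** "Overall effectiveness rate is defined as the proportion of patients whose SAS and SDS scores have reduced by more than 25%, the primary endpoint". The assumed rates come from the centre's experience: "at the third follow-up visit, we found that the overall effectiveness rate was approximately 75% in the WeChat peer support group". For the control arm the assumed figure is 60%.

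On the test level, section 2.12 says: "In all statistics, a 2-tailed alpha of 0.05 was employed".

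**The concern.** A comparison of scores and a comparison of responder proportions are different quantities. Under section 2.12 they also get different tests (t-test or Mann-Whitney for quantitative variables, chi-square or Fisher for categorical ones), and they can disagree. If the document does not say which form, scale and visit is primary, more than one result can later be presented as the primary one, each tested at 0.05.

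This matters more here because neither participants nor investigators are blinded (section 2.9) and SAS and SDS are self-rated (section 2.2). An endpoint fixed in advance is one of the few safeguards such a design has. In the other direction, if success needs a separate win on each scale, the power calculated for one rate overstates the power of the trial.

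The extra measurement in Table 1 is also a practical problem: sites cannot tell whether to send the questionnaire after delivery.

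**Working it through.** **1. The statements side by side**

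| Place | Form | Number of endpoints | Visit for the primary | Post-baseline SAS/SDS |
|---|---|---|---|---|
| Abstract | levels | two | none fixed | 3 |
| Table 1 | levels (scores) | two | none fixed | 4 |
| 2.8 | >25% responder rate | one rate, called measures in the plural | none fixed | 3 |
| 2.11 | >25% responder rate | one | third follow-up, only as source of the rates | not listed |

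The two sections that define the endpoint agree on its form. They do not settle the visit, or whether one patient must improve on both scales.

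**2. The plan's own figure**

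Inputs from 2.11: 75% v 60%, level 0.05, power 0.80, dropout 20%. The unpooled formula per arm is n = (z_alpha + z_beta)² × [p1(1−p1) + p2(1−p2)] / (p1−p2)².

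- Variance term: 0.75×0.25 + 0.60×0.40 = 0.4275. Squared difference: 0.0225.
- One-sided 0.05: (1.645 + 0.842)² × 0.4275 / 0.0225 = 117.5, so 118 per arm and 236 in total.
- Dropout: 118/0.8 = 147.5, so 148 per arm and 296 in total.

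This reproduces 236 and 296. The size is therefore that of **one** comparison of **one** rate. Two-sided 0.05 gives 149.1, so 150 per arm and 300 in total. The plan's figure thus rests on a one-sided test, which is a separate point.

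**3. Error rate if any scale at any visit could be claimed**

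The documents state no such rule, so this is a conditional calculation. For k independent two-sided tests at 0.05 the chance of at least one false positive is 1 − 0.95^k. For correlated tests I simulated multivariate normal test statistics under no effect (300,000-400,000 draws). Correlation was the same between scales and between visits, and |Z| > 1.96 counted as significant. The documents give no correlation, so 0.3-0.8 is assumed.

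| Tests | Independent | Correlation 0.3 | 0.5 | 0.7 | 0.8 |
|---|---|---|---|---|---|
| 2 scales × 1 visit (k=2) | 9.8% | 9.5% | 9.0% | 8.4% | 7.9% |
| 2 scales × 3 visits (k=6) | 26.5% | 24.7% | 22.0% | 17.7% | 14.9% |
| 2 scales × 4 visits (k=8) | 33.7% | 31.1% | 26.8% | 20.9% | 17.1% |

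Counting only results that favour peer support roughly halves these, to about 4-5%, 7-13% and 9-16% over the same correlations, against an intended 2.5%.

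**4. Power if each scale has its own rate and both must win**

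Take the stated 80% for each scale. Joint power is the bivariate normal probability that both statistics exceed their critical values.

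- Correlation 0: 0.80 × 0.80 = 64%.
- Correlation 0.5: 69%.
- Correlation 0.9: 75%.

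Section 2.11 gives no rates by scale, so 80% for each is itself an assumption.

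**The case against.** The strongest reply is that the protocol does fix its endpoint. Section 2.8 equates improvement with the overall effectiveness rate, and 2.11 calls that rate the primary endpoint, in the singular. The abstract can be read as naming the domain in short form, and Table 1 as naming the instrument collected. The comparisons of ratings come after the definition and may be meant as descriptive. This stands in part: the responder rate is the best-supported reading. But Table 1 and the abstract do not carry it, nothing makes the rating comparisons secondary, and the visit and the treatment of the two scales stay open even within 2.8 and 2.11.

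A second reply is that multiplicity control belongs in an analysis plan that is not shown. That is right about the method, and its absence is not counted here. Which result is primary is a protocol matter, and the conflicting statements are in this document.

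A reader might infer more than the text supports in three ways:

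- **That any single significant test counts as success.** No section says so. The error rates above are conditional on that reading.
- **That the sample size was built on a fall in both scales at the third follow-up.** Section 2.11 names that visit only as where the assumed rates were seen, and its wording does not settle whether both scales must fall in one patient.
- **That joint power is only 48-63%.** That figure starts from about 70% power per scale, which brings in the one-sided basis of the 236. At the stated 80% it is 64-75%.

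**Conclusion.** The inconsistency is real and needs correction before analysis. As written, the protocol does not determine which form of the endpoint, at which visit, and on one or both scales, decides the trial. It also contradicts itself on whether SAS and SDS are measured after delivery. These conclusions rest on the text alone.

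The size depends on the reading. If the trial is held to one responder rate at one visit, the 5% level stands. If any scale at any visit could be claimed, the two-sided false-positive chance is about 8-9.5% (one visit), 15-25% (three visits) or 17-31% (four visits), and about half that in favour of peer support. If separate wins on both scales are needed, joint power is 64-75% rather than 80%. The error rates assume correlations of 0.3-0.8 and the joint power 0-0.9; the documents give none.

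**What to change.** State one primary endpoint in the same words in the abstract, Table 1, 2.8 and 2.11: the proportion with a fall of more than 25% from baseline at the third follow-up (27-29 weeks), the visit from which the assumed rates were taken, tested once at two-sided 0.05. The sponsor should state whether a patient must improve on both SAS and SDS, which is the natural reading of the single rate in 2.11, or whether each scale has its own rate.

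If two rates are meant, either require both or split alpha, and restate the power. As an illustration, with 75% v 60% assumed on each scale and 0.025 each, the pooled two-proportion formula gives 185 per arm (370 evaluable). With 20% dropout that is 185/0.8 = 231.25, so 232 per arm and 464 in total.

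Label the SAS and SDS scores, the other visits and the longitudinal comparison as secondary. Reconcile Table 1 with 2.7 and 2.8 on the post-delivery questionnaire.

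For a single combined rate this is a change of wording. The price is giving up confirmatory claims at other visits and on single scales. It does not cure the one-sided basis of the sample size: at two-sided 0.05, 236 evaluable patients give about 69% power. That needs its own correction.

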### 2.2. Data collection

Both groups of patients are required to provide baseline information, including sociodemographic characteristics, disease history, and social behavioral characteristics such as smoking and alcohol use. Collect and complete the self-rating anxiety scale (SAS), which consists of 20 items overall, of which 5 indicate positive emotional experience and 15 negative emotional experience; the greater the score, the more anxious the patient is; the score below 50 represents normal, while mild will be anxiety score of 50 to 59, moderate anxiety 60 to 69, severe anxiety 70 points or more, and self-rating depression scale (SDS) (a total of 20 items; the greater the score, the higher the level of anxiety). Less than 50 points are considered normal, 50 to 59 points are considered mild anxiety, 60 to 69 points are considered moderate anxiety, and more than 70 points are considered severe anxiety during the course of treatment.

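### The primary endpoint cuts the SAS and SDS scores to a yes/no fall of more than 25%, which usually costs power: about 20 points for one normal score, and 0 to 16 points if both scales must succeed.

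*Protocol article*

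**What the plan says.** Section 2.8 defines the primary measure as an "overall effectiveness rate, defined as the proportion of patients with a decreases of more than 25% in SAS" and SDS. Section 2.11 repeats it: "Overall effectiveness rate is defined as the proportion of patients whose SAS and SDS scores have reduced by more than 25%, the primary endpoint". The rates used for sizing are "approximately 75% in the WeChat peer support group and about 60% in the routine intervention group", and they refer to the third follow-up, which is the visit at 27 to 29 weeks. The calculation was made "with a hypothesis test level of 0.05 and a test power of 0.8". It gave 236 women, raised to 296 (148 per arm) for 20% dropout.

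The underlying data are graded. Section 2.2 describes SAS as a 20-item score: "the greater the score, the more anxious the patient is; the score below 50 represents normal". It treats SDS in the same way. Table 1 schedules both scales at baseline and at every follow-up. Entry requires at least 50 on each (section 2.3.1).

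The scores also have a place in the plan. The abstract and Table 1 list anxiety and depression levels as primary. Section 2.8 compares the ratings between groups at each visit. Section 2.12 says that "quantitative variables were examined using the independent samples t-test or Mann–Whitney" *U* test, with all tests two-tailed at 0.05.

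**The concern.** A percentage cut treats a 24% fall like a worsening, and a 26% fall like a 50% fall. It also sits awkwardly with the article's own bands:

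- A fall from 70 to 52 is 18/70 = 25.7%, a success, although 52 is still in the mild band.
- A fall from 50 to 38 is 12/50 = 24%, a failure, although 38 is well inside normal. A woman who enters at 50 must score below 37.5 to count.

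The stated aim is to improve anxiety and depression. If the main test uses the coarser form of data that the trial already holds, a real effect is more likely to be missed, with no saving in visits or patients.

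**Working it through.** **Inputs.** Rates 0.75 and 0.60, alpha 0.05, power 0.80, 236 before and 296 after dropout (2.11); two-tailed testing (2.12); 1:1 allocation (2.9). The documents give no SD, mean change or SAS-SDS correlation, so the distribution shapes and correlations below are assumptions.

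**1. Reproducing 236.** Unpooled formula: n per arm = (z_alpha + z_power)² × [0.75×0.25 + 0.60×0.40] / 0.15², where 0.4275/0.0225 = 19.

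- One-sided 0.05: (1.645 + 0.842)² × 19 = 117.5, so 118 per arm, or 236. This matches.
- Two-sided 0.05: (1.960 + 0.842)² × 19 = 149.1, so 150 per arm, or 300. The pooled and arcsine forms give 304, and the continuity-corrected form gives 330. None matches.
- Dropout: 118/0.8 = 147.5, so 148 per arm, or 296. This matches.

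**2. Power of the yes/no test.** With 118 per arm and two-sided 0.05, exact enumeration of the uncorrected chi-square test gives 0.696 (normal approximation 0.694). Reaching 0.80 takes 152 per arm.

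**3. One score, normal percent change, equal SD.** The two rates imply a shift d = z(0.75) − z(0.60) = 0.6745 − 0.2533 = 0.421 SD. The noncentrality is 0.421 × √(118/2) = 3.23. Power is 0.896 by the noncentral t and 0.899 by the normal approximation. About 90 per arm would give 0.80.

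| Setting | Yes/no | One score | Gain |
|---|---|---|---|
| 118 per arm, two-sided | 0.694 | 0.899 | 20.5 points |
| 148 per arm, two-sided | 0.790 | 0.952 | 16.2 points |
| 118 per arm, one-sided | 0.796 | 0.944 | 14.9 points |

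(All normal approximation.)

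**4. Both scales.** Read literally, the endpoint needs SAS and SDS both to fall by more than 25%. For each assumed correlation rho, a common threshold was solved so that the bivariate normal probability of passing both is 0.75 in one arm and 0.60 in the other. The difference is the per-scale shift d. The average of the two changes then has standardised shift d/√((1+rho)/2). For example, at rho 0.3 it is 0.374/√0.65 = 0.464. Power at 118 per arm, two-sided 0.05:

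| rho | d per scale | Both scales significant | Gain over 0.696 | One test on the average | Gain over 0.696 |
|---|---|---|---|---|---|
| 0.3 | 0.374 | 0.696 | 0 | 0.944 | 25 points |
| 0.5 | 0.388 | 0.752 | 6 points | 0.929 | 23 points |
| 0.7 | 0.401 | 0.804 | 11 points | 0.915 | 22 points |
| 0.9 | 0.415 | 0.856 | 16 points | 0.902 | 21 points |

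**5. Other shapes, one score, 118 per arm.** Here d = [F⁻¹(0.75) − F⁻¹(0.60)]/SD, with change taken as follow-up minus baseline so that a fall is negative.

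- Logistic: d = 0.382, power 0.83.
- t with 5 df: d = 0.356, power 0.78, a gain of about 8 points.
- Right-skewed Gumbel: d = 0.448, power 0.93.
- Left-skewed Gumbel (long tail of large falls): d = 0.323, power 0.69, no gain.

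**The case against.** A responder rate is a legitimate and readable primary endpoint, and nothing in the article is miscalculated because of it. The scores are not ignored either, since section 2.8 compares them and the abstract and Table 1 call the levels primary. That stands: this is a design choice that can be improved, not an arithmetic error.

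A reader might draw three stronger conclusions that the documents do not support.

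- **That the cut costs a flat 20 points.** That figure belongs to one normal score at 118 per arm, two-sided. The endpoint joins two scales. If both must be significant, the gain is 0 to 16 points. Only the averaged test reaches 20 or more, and it does so by relaxing the requirement that each scale succeed.
- **That the cut is why power is only about 70%.** It is not. The trial was planned for 80%, and the shortfall arises because 236 matches a one-sided 0.05 while section 2.12 tests two-sided. At the one-sided level the yes/no test has its 80%, and the cut still costs about 15 points for one normal score.
- **That 25% is arbitrary.** Section 2.8 attaches a reference to the cut for each scale, and those sources are not at hand. The band examples show only that the cut does not mark recovery. The article claims improvement, and a mean difference does not mark recovery either.

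One technical caution also stands. The powers are for percent change. A simulation with assumed baselines from 50 upward and percent-change SDs of 0.10 to 0.20 gave 0.85 to 0.88 for change in points, against 0.89 for percent change. This is a modest loss.

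**Conclusion.** The point holds in a qualified form. The primary test and the sample size rest on a dichotomy of two scores that the trial already records, and analysing the scores would usually be more powerful. With the article's rates, 118 evaluable per arm, two-sided 0.05 and normal changes with equal SD, power rises from about 70% to about 90% for one score and to 90 to 94% for the averaged change. With both scales required it is 70 to 86%. The gain for one score is smaller with more evaluable women (about 16 points at 148 per arm), with one-sided alpha (about 15) or with heavy tails (about 8), and it can vanish under marked left skew. All of this depends on an SD, a shape and a correlation that the article does not give, so confidence in the size is medium. The one-sided/two-sided sizing mismatch is a separate matter and should be corrected on its own account.

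**What to change.** Amend sections 2.8, 2.11 and 2.12 as follows.

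- Make the primary comparison one test of the between-group difference in the average of the SAS and SDS changes from baseline at 27 to 29 weeks, and report each scale separately. State whether change is in points or percent.
- If success on both scales must be kept, require both differences to be significant at two-sided 0.05 and state the smaller gain (0 to 16 points under the assumptions above). This rule needs no split of alpha.
- Keep the more-than-25% effectiveness rate as a secondary endpoint.
- Keep 296 women, and state the power of the score comparison with its assumed SD and SAS-SDS correlation.

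The cost is a wording change, with no new data, visits or patients. There are two drawbacks: the headline becomes a mean difference instead of a success rate, and the averaged test can be carried by a large effect on one scale, which is why both scales should be shown beside it.

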**Secondary outcome**						
pregnancy outcome						
ectopic pregnancy			√	√	√	
miscarriage			√	√	√	
early pregnancy loss			√			
late pregnancy loss			√	√	√	
premature birth						√
live birth						√

SAS = self-rating anxiety scale, SDS = self-rating depression scale.

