### 2.3. Eligibility criteria

#### 2.3.1. Inclusion criteria.

Clinically pregnant women (i.e., fetal heartbeat or gestational sac at 6–9 weeks after embryo transfer^[39]^) undergoing IVF-ET.age 18 to 49 years old.SAS standard score ≥ 50 points (i.e., mild anxiety or above); SDS standard score ≥ 50 points (i.e., mild depression or above).Patients who own electronic devices such smartphones, tablets, or computers, have Internet access, and are skilled WeChat users.Have reading, writing, and comprehension abilities.Informed consent and willing participation for WeChat group-based peer support.

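### The miscarriage and live-birth definitions in section 2.8 overlap, the live-birth definition states no sign-of-life requirement, and late fetal death has no defined outcome

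*Protocol article*

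**What the plan says.** Section 2.8 of the protocol article states the role of these outcomes: "The secondary outcomes are comparisons of pregnancy outcomes, including ectopic pregnancy, miscarriage, as well as live birth". It then defines two of them by gestation and weight:

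- Miscarriage: "miscarriage is defined as termination of pregnancy at less than 28 weeks of gestation with a fetus weighing less than 1000 g".
- Live birth: "live birth is defined as at least 22 weeks of gestation or at least 500 g".

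Table 1 adds rows for early pregnancy loss, "late pregnancy loss" and premature birth, none of which section 2.8 defines. Miscarriage and late loss are scheduled at the three pregnancy visits, the last at 27–29 weeks. Of the pregnancy outcomes, only premature birth and live birth are scheduled for the assessment within 3 days of delivery. There is no row for stillbirth or fetal death.

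**The concern.** Miscarriage is an unfavourable result and live birth a favourable one, so a pregnancy should not be able to count as both. The stated limits differ (28 weeks and 1000 g for one, 22 weeks and 500 g for the other), which leaves a band where both apply. Neither definition mentions whether the infant was alive, so vital status cannot settle which one applies.

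At stake are the live-birth and miscarriage counts in each arm. Better pregnancy outcomes are among the trial's stated aims (Abstract and section 3), and they make up the whole set of secondary outcomes. Without a fixed rule, very early deliveries and late fetal deaths would have to be classified case by case after the event.

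**Working it through.** The plan states no figure to reproduce here; the check is on the logic of the two definitions.

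**Step 1: write the definitions as rules.** With GA for gestation in weeks and W for weight in grams, both from section 2.8:

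- Miscarriage: GA < 28 **and** W < 1000.
- Live birth: GA ≥ 22 **or** W ≥ 500.

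**Step 2: intersect them.** Both hold when GA < 28, W < 1000, and either GA ≥ 22 or W ≥ 500. This splits into two regions:

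- 22 ≤ GA < 28 with W < 1000;
- GA < 22 with 500 ≤ W < 1000.

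**Step 3: test cases.**

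| Gestation, weight | Meets miscarriage rule | Meets live-birth rule |
|---|---|---|
| 20 weeks, 300 g | yes | no |
| 20 weeks, 550 g | yes | yes |
| 22 weeks, 450 g | yes | yes |
| 24 weeks, 600 g | yes | yes |
| 27 weeks, 950 g | yes | yes |
| 27 weeks, 1050 g | no | yes |
| 28 weeks, 900 g | no | yes |
| 38 weeks, 3000 g | no | yes |

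Four of these eight cases meet both rules.

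**Step 4: vital status.** It enters neither rule. Take a fetal death at 38 weeks and 3000 g. It is not a miscarriage, because GA ≥ 28. Either it meets the live-birth rule as literally worded, or, if the label itself is taken to require a living infant, it meets no defined outcome. Table 1 does not fill the gap: its loss rows stop at the 27–29 week visit, and late pregnancy loss is undefined.

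**Step 5: size.** The article gives no rate for deliveries in the overlap or for fetal deaths from 22 weeks. Assume that together they affect 0.5% to 2% of women. With 148 per arm (section 2.11):

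- 0.005 × 148 = 0.74;
- 0.02 × 148 = 2.96.

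That is about 1 to 3 women per arm, or at most 2 percentage points of an arm's live-birth proportion. For comparison, the 95% half-width for a difference between two arms of 148 is 1.96 × √(2p(1 − p)/148). Assuming live-birth proportions p of 90% and 60%, this gives about 7 and 11 percentage points.

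**The case against.** The strongest reply is that the term being defined is live birth. On an ordinary reading the word *live* already supplies the vital status, and the clause only adds the limit above which a birth counts. A reader might infer from the literal wording that stillbirths will be reported as successes. The document does not support that as a certainty; what it shows is an incomplete definition. This part of the reply stands.

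It does not remove the overlap. An infant born alive at 24 weeks and 600 g still meets both rules if termination of pregnancy covers any ending of the pregnancy, and the text does not restrict it. Nor does it give a fetal death at 38 weeks an outcome to belong to.

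Other limits on the point also stand:

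- A reader might infer that the categories were meant to add up to the number randomised and fail to. The article never claims this. It lists separate endpoints, and the word *including* in section 2.8 leaves the list open.
- Table 1 is captioned as a template, and an article may leave form details to the full protocol. The missing loss entry after delivery is therefore supporting evidence, not a defect by itself.
- The definitions apply equally to both arms, and section 2.9 plans blinded outcome assessors. No bias in favour of one arm is shown.
- A reader might also want ectopic pregnancy removed from the outcomes and treated as an eligibility failure. That does not follow. The inclusion criterion asks for "fetal heartbeat or gestational sac at 6–9 weeks after embryo transfer" and states no location, and such relabelling could invite removal of women after randomisation.

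The format of a condensed article does not excuse the central defect. The two limits are printed, and they conflict as printed.

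**Conclusion.** The overlap follows from the two definitions alone and needs no assumption beyond reading termination of pregnancy as any ending of it. The same delivery can be counted as both a miscarriage and a live birth, and nothing in the article says which takes precedence. The missing sign-of-life requirement and the lack of a defined outcome for fetal death at or after 28 weeks are gaps in the same set of definitions.

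The consequence is limited. Only secondary outcomes are affected; the primary endpoint and the sample size rest on the anxiety and depression scores. The figure of 1 to 3 women per arm depends entirely on the assumed 0.5% to 2%. It would be smaller if fetal deaths are kept out of live birth by the ordinary reading of the label. These are nevertheless among the most serious events the trial will record. The point is a moderate correction, best made before any pregnancy outcome is classified.

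**What to change.** In section 2.8:

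1. Choose one common gestation and weight limit for both definitions. The present forms already fit together: below the limit on both measures, against at or above it on either. With the same two thresholds in each, they meet without gap or overlap. Which limit to adopt is for the sponsor to decide and state.
2. Define live birth as at least one infant born with signs of life at or above that limit.
3. Define stillbirth or late fetal death as its own outcome at or above the limit, with no infant born alive.
4. State that each randomised woman's pregnancy is classified once, with a category for unknown outcome, and say where early and late pregnancy loss fall.

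In Table 1, add stillbirth or late fetal death to the assessment within 3 days of delivery.

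The cost is a few reworded sentences, one table row and one field on the delivery form. No change to the sample size, the primary analysis or the visit schedule is needed.

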In conclusion, we design this randomized controlled study to examine whether an intervention based on WeChat group peer support can improve anxiety, depression, and pregnancy outcomes in pregnant women following IVF-ET. This is done to ensure the medical conditions of patients under special circumstances.

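### Section 2.8 defines miscarriage and live birth so that they overlap, and states no sign of life for live birth, so some pregnancies fit two opposite secondary outcomes and late fetal deaths have no clear place

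*Protocol article*

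**What the plan says.** Section 2.8 (Outcomes) sets the role of these endpoints: "The secondary outcomes are comparisons of pregnancy outcomes, including ectopic pregnancy, miscarriage, as well as live birth". The definitions follow in one sentence:

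- Miscarriage: "miscarriage is defined as termination of pregnancy at less than 28 weeks of gestation with a fetus weighing less than 1000 g".
- Live birth: "live birth is defined as at least 22 weeks of gestation or at least 500 g".

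Table 1 lists further pregnancy outcomes that 2.8 does not define, among them "late pregnancy loss" and "premature birth". Miscarriage and late loss are ticked at the three visits up to 27–29 weeks. Premature birth and live birth are ticked only within 3 days after delivery. Stillbirth is neither defined nor listed, and no section says which category prevails when a pregnancy fits more than one.

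The closing paragraph of section 3 (Discussion) says the trial will examine whether the intervention "can improve anxiety, depression, and pregnancy outcomes in pregnant women following IVF-ET".

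**The concern.** Miscarriage and live birth are opposite results of a pregnancy, and a reader of the trial report will expect each woman to appear in at most one of them. The two rules use different limits: 28 weeks and 1000 g as the ceiling for miscarriage, 22 weeks or 500 g as the floor for live birth. The floor lies below the ceiling, so there is a band in which both apply. The conditions are also joined differently: miscarriage needs both of its conditions, while live birth needs only one.

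The live-birth rule is a threshold of duration or weight only. Nothing in it separates a living infant from a fetal death past the threshold.

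At stake is whether the comparison of pregnancy outcomes can be interpreted and reproduced. If the rules are applied as printed, a woman can count both for and against the intervention. If assessors resolve the conflict themselves, the rule they use is not the one published. The article states these rules outright, so this is not a matter of detail left to a fuller document.

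**Working it through.** The article gives no figure to reproduce here; the check is one of logic. Let G be gestation in completed weeks at the end of pregnancy and W the fetal or birth weight in grams.

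**Rules as written in 2.8**

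- Miscarriage: G < 28 and W < 1000.
- Live birth: G ≥ 22 or W ≥ 500.

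**Overlap.** Both hold when (G < 28 and W < 1000) and (G ≥ 22 or W ≥ 500). This splits into two regions:

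1. 22 ≤ G < 28 with W < 1000;
2. G < 22 with 500 ≤ W < 1000.

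**Illustrative cases**

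| Weeks / weight | Miscarriage rule | Live-birth rule | Result |
|---|---|---|---|
| 20 / 350 g | met | not met | miscarriage only |
| 21 / 520 g | met | met | both |
| 22 / 450 g | met | met | both |
| 24 / 650 g | met | met | both |
| 26 / 900 g | met | met | both |
| 27 / 1050 g | not met | met | live birth only |
| 32 / 1700 g | not met | met | live birth only |

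The weight condition matters: at 22 to 27 weeks the overlap stops at 1000 g.

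**Does a charitable reading remove the problem?** Four events under three readings:

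| Event | Literal | Life required for live birth | Life required, and miscarriage limited to fetal deaths |
|---|---|---|---|
| Fetal death, 24 wk / 650 g | both | miscarriage | miscarriage |
| Live-born, 24 wk / 650 g | both | both | live birth |
| Fetal death, 27 wk / 1050 g | live birth | none | none |
| Fetal death, 32 wk / 1700 g | live birth | none | none |

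On the first two readings the categories are not mutually exclusive. On the second and third they are not exhaustive. No reading gives both.

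**Size.** The document gives no rate of loss or birth at 22–27 weeks and no stillbirth rate. The following rates are assumptions, used only to show the order of magnitude among 296 women (148 per arm):

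- If 1–2% of pregnancies end at 22–27 weeks: 296 × 0.01 = 3.0 to 296 × 0.02 = 5.9 women. Under the literal reading this is a ceiling for region 1, because those at 1000 g or more drop out.
- If life is required for live birth, and 0.5–1.5% are live-born at 22–27 weeks: 148 × 0.005 = 0.7 to 148 × 0.015 = 2.2 women per arm in region 1, again before the weight condition is applied.
- If 0.3–1% are fetal deaths at or after 28 weeks: 296 × 0.003 = 0.9 to 296 × 0.01 = 3.0 women, who are either scored as live births (literal reading) or left unclassified.

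**The case against.** The strongest reply is that the term being defined is *live* birth. On its natural reading, 22 weeks or 500 g is the point from which a birth that is live gets counted, and an assessor would have to ignore the term itself to score a fetal death at 32 weeks as a success. Section 2.9 says outcome assessors are blinded, so any misreading should not favour one arm. That is a fair reply. A reader might infer from the missing sign-of-life phrase that stillbirths will routinely be counted as live births and that a sizeable share of failures will be hidden. The document does not support this: the inference needs the literal reading and rates that appear nowhere in the article.

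A reader might also infer from Table 1 that a death after the third visit can only be entered as a live birth. That does not follow. The live-birth row at delivery can be answered no, and section 2.13 provides record cards that include emergency events. Nor is it a contradiction that a premature birth can also be a live birth.

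Finally, all of these are secondary outcomes. The Abstract names anxiety and depression as primary, and section 2.11 sizes the trial on the response in the anxiety and depression scores. Section 2.8 does not rank live birth above the other pregnancy outcomes, so it should not be called the main one.

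What the reply does not remove is shown in the second table above. Requiring life still leaves a live-born infant at 24 weeks and 650 g within both rules, unless the miscarriage rule is also narrowed beyond its wording. Even then, a fetal death at or after 28 weeks is in no outcome that 2.8 defines. The undefined late-loss row does not settle the matter, since its limits are not stated and it is not ticked at delivery.

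**Conclusion.** The concern holds as an error in a stated rule. The definitions of miscarriage and live birth in 2.8 overlap at 22 to under 28 weeks below 1000 g, and before 22 weeks at 500 to 999 g. The live-birth definition states no sign of life, so a late fetal death is either admitted as a live birth or left without a defined outcome, depending on the reading.

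The overlap follows from the wording alone and rests on no assumption. Its numerical effect cannot be derived from the document. Under the assumed rates it is a handful of women among 296. No direction or size of bias in the arm comparison can be claimed, and the primary endpoint and the sample size are unaffected. The point should be fixed, but it does not threaten the trial's main result.

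**What to change.** In section 2.8:

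- Define live birth, per randomised woman, as at least one infant born with signs of life.
- Define miscarriage or pregnancy loss as a pregnancy that ends without a live-born infant.
- Reconcile the 22-week/500 g and 28-week/1000 g limits into one boundary, chosen by the sponsor and used in every definition. If weeks and weight are both kept, say which prevails when they disagree.
- Classify a fetal death at or after that boundary as stillbirth, not live birth, and one before it as miscarriage. State how a birth with signs of life before the boundary is counted.

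Record vital status at delivery, and show this in the delivery column of Table 1.

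The cost is a few sentences and one field on the delivery form. No extra women or visits are needed. The change should be made before any pregnancy outcome is classified.
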